In relation to the primary objective, the efficacy of the SLPC will be measured at 4 months after the beginning of chemotherapy treatment, corresponding to the ninth cycle of chemotherapy. As mentioned previously, chronic toxicity does not become apparent until cycles 8–10 in the commonly used FOLFOX dosing regimen. The study diagram is shown in Fig. 1.

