### Outcomes {12}

The primary endpoint is the rate of neurotoxicity according to US NCI (National Cancer Institute) criteria in both arms 4 months after the beginning of oxaliplatin-based regimen. NCI criteria are listed in Table 4.

**Table 4 Tab4:** US National Cancer Institute common toxicity criteria (NCI-CTC)

Oxaliplatine dosage adjustment according to neurotoxicity				
Neurotoxicities	Grade	Toxicity duration		
		1 to 7 days	> 7 days	Persistent between cycles^**a**^
Paresthesias/dysesthesias^b^ that do not interfere with fine motor skills	1	No dose reduction		
Paresthesias/dysesthesias^b^ that interfere with fine motor skills but do not affect activities of daily living (ADLs)	2	No dose reduction		75% of the dose
Paresthesias/dysesthesias^b^ with pain or decreased fine motor skills that affect activities of daily living (ADLs)	3	1st time: 75% of the dose 2nd time: 50% of the dose		Discontinue treatment
Persistent or incapacitating or lifethreatening paresthesia/dysesthesia	4	Discontinue treatment		
Acute toxicity: laryngeal-pharyngeal dysesthesia^b^ (during or within 2 h after infusion)	NA	Extend the oxaliplatin infusion to 6 h on the next treatment.	NA	

^a^Toxicity still present at the beginning of the next cycle

^b^May be caused by the cold

The secondary outcomes are:⇨ Time frame for definitive discontinuation or decrease in oxaliplatin treatment. The dose or discontinuation of oxaliplatin will be noted at each chemotherapy visit, in accordance with the process established in Table 3⇨ Dose intensity of oxaliplatin noted at each chemotherapy visit (see Table 3)⇨ Neurological adverse events at the following hospital visits: baseline, M4, and M9/termination visit⇨ Nerve electrodiagnostic examination (EDX) and neurology questionnaire: Overall Neuropathy Limitation Scale (ONLS) French translation according to Graham et Hugues [14] at baseline, M4 and M9/termination visit⇨ Adverse Events collected at each chemotherapy visit or in patient diary⇨ Quality of life questionnaire: QLQ C30 at baseline, M4 and M9/termination visit

Note that when a patient discontinues the study treatment early for whatever reason, an early termination visit will be conducted if the patient’s condition allows.

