### Sample size {14}

Simon’s two-stage design [15] will be used. The null hypothesis that the true response rate is 0.60, the proportion of neurotoxicity targeted, will be tested against a one-sided alternative. In the first stage, 31 patients will be accrued. If there are 18 patients or fewer with grade 1 neurotoxicity among these 31 patients in the SLPC arm, the study will be halted. Otherwise, 24 additional patients will be accrued, making a total of 55. The null hypothesis will be rejected if 38 or more responses are observed in 55 of the SLPC arm patients. With a type I error rate of 0.05 and a power of 0.90, 55 patients will be enrolled in each arm, that is to say, 110 patients.

All the previous hypotheses account for a lost-to-follow-up rate at 4 months of 20%.

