### Plan to promote participant retention and complete follow-up {18b}

The target population of the trial is cancer patients during chemotherapy treatment; missing data could only result from withdrawal of consent or a serious adverse event (SAE). There is no plan for promoting participant retention.

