## Statistical methods

### Statistical methods for primary and secondary outcomes {20a}

Descriptive analyses will be conducted for all variables collected. Point estimates and 95% confidence intervals will be calculated for qualitative and quantitative variables. For estimates obtained using a small sample, the medians and interquartile intervals (for quantitative variables) and exact confidence interval (for qualitative variables) will be provided. All analyses will be performed with the use of R software (version 4.0) or SAS software (version 9.4).

To fulfill the main objective of this study, the prevalence of neurotoxicity of grade 2 or above in both arms will be estimated using linear mixed regression, taking into account the center effect (random effect). The second step will be to adjust this estimate based on known risk factors (gender, age, etc.).

For the secondary analyses:Comparison of time before cessation or reduction of chemotherapy treatment will be estimated using the Kaplan-Meier method and tested with the log-rank test;Comparison of patients with a decrease in treatment due to neurological toxicity will take place via mixed linear regression on both treatment arms;Progression of grades 3 and 4 neurological adverse events at baseline, M4, and M9 (or at the last visit if earlier) will be tested using mixed linear regression with a random center effect;EDX data will be compared using Fisher’s exact test and the Wilcoxon-Mann-Whitney test;The chi-square test or Fisher’s exact test will be used to compare Adverse Events in both arms;Progression of grades 3 and 4 neurological QLQ C30 at baseline, M4, and M9 (or at the last visit if earlier) will be tested via mixed linear regression with a random center effect; andMedian progression-free survival will be estimated and plotted using the Kaplan-Meier method and the response rate will be estimated as a percentage with a 95% confidence interval.

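### Letting the last visit stand in for month 9 pools early values with true month-9 values in the neurological adverse-event and QLQ-C30 analyses

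*Protocol article*

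**What the plan says.** Statistical methods {20a} of the protocol article lists, among the secondary analyses, "Progression of grades 3 and 4 neurological adverse events at baseline, M4, and M9 (or at the last visit if earlier"), tested by mixed linear regression with a random center effect. The quality-of-life item carries the same clause: "QLQ C30 at baseline, M4, and M9 (or at the last visit if earlier) will be tested via mixed linear regression with a random center".

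Outcomes {12} defines the last time point in the same way: "Neurological adverse events at the following hospital visits: baseline, M4, and M9/termination visit". It adds that "when a patient discontinues the study treatment early for whatever reason, an early termination visit will be conducted if the patient’s condition allows". The closing assessment of an early leaver can therefore fall at any time before M9.

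Three other places bear on the point:
- Explanation for the choice of comparators {6b} says that "chronic toxicity does not become apparent until cycles 8–10 in the commonly used FOLFOX dosing regimen".
- Sample size {14} states: "All the previous hypotheses account for a lost-to-follow-up rate at 4 months of 20"%. No loss figure is given for M9.
- The section on retention {18b} says that "missing data could only result from withdrawal of consent or a serious adverse event (SAE").

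The section on missing data {20c} reserves multiple imputation for the primary objective.

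**The concern.** A last-visit rule treats a value taken part-way through treatment as if it were the month-9 result. That amounts to assuming no change after the patient leaves, which sits badly with an outcome that the article itself describes as cumulative and late.

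Nothing stated for these two outcomes offsets the rule. Imputation does not extend to them, actual visit time is not said to be modelled, and center is the only random effect named.

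At stake is the M9 comparison of neurological toxicity and quality of life. Objectives {7} lists both among the comparisons between arms, although Trial design {8} calls the trial non-comparative. If the outcome moves between the early visit and M9, a real difference can be diluted. If one arm loses more patients, or loses them sooner, a difference can arise from the rule alone.

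**Working it through.** The plan gives no figure for this rule, so there is none to reproduce. Two checks can be made.

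**1. Does the substituted value represent month 9?**

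Inputs: oxaliplatin 85 mg/m² per cycle (text after Table 2); 12 induction cycles (Intervention description {11a}); M4 visit on day 1 of cycle 9 (Table 2); symptoms more likely once the cumulative dose passes 780–850 mg/m² (Discussion).

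Cumulative dose = 85 × cycles given at full dose:
- at M4, before the cycle 9 infusion: 8 × 85 = 680 mg/m²
- after cycle 9: 9 × 85 = 765 mg/m²
- after cycle 10: 10 × 85 = 850 mg/m²
- after cycle 12: 12 × 85 = 1020 mg/m²

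A last visit up to M4 lies below the article's own dose range. A patient reaching M9 after 12 full-dose cycles lies above it. For such early leavers the substituted neuropathy value will tend to be lower than the M9 value. A patient leaving between cycle 10 and cycle 18 is already in or past that range, so the argument does not carry over.

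**2. How large could the effect be?**

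For each arm, with a fraction d of values substituted:

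scored M9 mean = (1 − d) × true M9 mean + d × early mean

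This takes leavers to have had, on average, the same M9 value as completers. All outcome values and arm-specific fractions below are assumptions.

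*QLQ-C30, real effect.* Assume a change at M9 of −15 (placebo) and −5 (SLPC), one fifth of it present early (−3 and −1). The true difference is 10 and the early difference is 2:
- d = 20% in both arms: 0.8 × 10 + 0.2 × 2 = 8.4
- d = 30%: 0.7 × 10 + 0.3 × 2 = 7.6
- d = 40%: 0.6 × 10 + 0.4 × 2 = 6.8

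*QLQ-C30, no effect.* Assume −15 at M9 and −3 early in both arms, with 20% (placebo) and 40% (SLPC) substituted:
- placebo: 0.8 × (−15) + 0.2 × (−3) = −12.6
- SLPC: 0.6 × (−15) + 0.4 × (−3) = −10.2
- spurious difference: 2.4 points. With equal fractions it is 0.

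*Grade 3–4 events, no effect.* Assume 10% at M9 and 2% early, with the same 20% and 40%:
- placebo: 0.8 × 10 + 0.2 × 2 = 8.4%
- SLPC: 0.6 × 10 + 0.4 × 2 = 6.8%
- spurious difference: 1.6 percentage points.

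*Unequal dropout with a real effect can move the result either way.* Take a more common binary outcome with assumed M9 rates of 60% and 30% (true difference 30 points) and early rates of 20% and 10%:
- 30% of control and 10% of SLPC values substituted: (0.7 × 60 + 0.3 × 20) − (0.9 × 30 + 0.1 × 10) = 48 − 28 = 20 points
- 10% of control and 30% of SLPC values substituted: (0.9 × 60 + 0.1 × 20) − (0.7 × 30 + 0.3 × 10) = 56 − 24 = 32 points

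**The case against.** The strongest reply is that the clause only names the visit that closes follow-up for an early leaver, and that the coding of time belongs to an analysis plan that is not shown. Part of this stands: the article does not say how time enters the model, nor that one cycle 9 value would be used for both M4 and M9. But the clause appears in both items, and Outcomes {12} treats M9 and the termination visit as one time point. As written, early values are analysed with the M9 values.

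Three stronger readings are tempting, and the documents do not support them.

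- *A reader might infer that substituted values are always too favourable.* Later leavers exit during or after the window in which chronic toxicity appears. Treatment may be stopped for unacceptable toxicity {11b}, and missing data are attributed to withdrawal of consent or SAEs, so some leavers may be recorded at their worst. Oxaliplatin induction ends at cycle 12, and the article does not show that grades only rise up to M9. For QLQ-C30, a general scale, it gives no time course at all.
- *A reader might infer at least 0.20 × 55 = 11 substituted values per arm.* The 20% is loss to follow-up at 4 months. A lost patient may have no termination visit, which is held only if the patient's condition allows, and Table 2 schedules QLQ-C30 only at inclusion, M4 and end of study. The number substituted is unknown.
- *A reader might infer that the stated mixed model makes the substitution unnecessary.* With only a center effect it does not link a patient's own visits, so deleting the clause would not by itself give protection under missing-at-random.

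It is also fair to say that these are secondary outcomes in a trial not powered for comparison between arms. That limits the weight of the point but does not justify the rule.

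**Conclusion.** The point holds, as a secondary-analysis matter that should be corrected. The stated rule pools last-visit values from differing times with true M9 values for neurological adverse events and QLQ-C30, and no stated method offsets this.

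For neuropathy in patients leaving before about cycles 8–10, the substituted value will tend to understate the M9 value. This rests on the article's own account of onset and cumulative dose. For other leavers and for QLQ-C30, the direction is open.

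Neither the number of substitutions nor the size of the bias can be derived from the documents. On the assumed inputs, equal substitution of 20% to 40% takes a 10-point QLQ-C30 difference down to between 8.4 and 6.8. Substitution of 20% against 40% creates about 2.4 points from nothing. For grade 3–4 events the bias is smaller in absolute terms (1.6 percentage points on the assumed rates). With no treatment effect and the same dropout and timing in both arms, the difference is not biased.

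The primary endpoint at M4 and the sample size are not touched.

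**What to change.** In both items of Statistical methods {20a}:
- Delete the clause that admits the last visit when it is earlier than M9.
- Analyse as M9 only values measured within a defined M9 window.
- Keep early-termination values in the analysis at their actual time.
- Use a repeated-measures mixed model with a patient-level random effect or a within-patient covariance structure, in addition to center. For binary grade 3–4 events use a generalised mixed model. State that the analysis is valid under missing-at-random.
- Keep the last-visit version as a sensitivity analysis only, and add one sensitivity analysis for informative dropout, since the stated reasons for missing data make it plausible.

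The pooled M9/termination time point in Outcomes {12} should be reworded to match.

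Cost: a wording change in two analysis items and one outcome definition, a little more analysis work, and slightly larger standard errors at M9 because substituted values no longer count as observed. No new data are needed.

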### Trial design {8}

PROPERTY is a non-comparative, randomized (ratio 1:1), double-blind, multicenter placebo-controlled study. The trial was constructed like a phase 2 drug trial and is not powered for direct comparison between the two arms.

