• Male or female with the age > or = to 18 years old. • Negative pregnancy test for women with child-bearing potential if applicable (without hysterectomy for example) • Information given to the patient who must have signed informed consent • Patient with Histologically or cytologically proven gastrointestinal adenocarcinoma including oesogastric, colorectal, and pancreatic cancers and planned to be treated with oxaliplatin • Patient with metastasic disease not previously treated • Previous radiotherapy is authorized if discontinued ≥15 days prior to randomization • Sites of disease evaluated within 42 days prior C1 day 1 of chemotherapy with thoracic-abdominal-pelvic CT scan (or abdominal-pelvic MRI and chest X-ray) • Patient with ECOG Performance status 0 or 1 • Patients with a Life expectancy ≥12 weeks • Laboratory results: ° Hematologic function: ▪ Polynuclear neutrophils ≥ 1.5.10^9^/L ▪ Platelets ≥100.10^9^/L ▪ Haemoglobin ≥9 g/dL ° Hepatic function: ▪ Transaminases ≤2.5 times upper limit of normal (ULN) (≤5 ULN in case of hepatic metastases), ▪ Alkaline phosphatases ≤2.5 × ULN (≤5 ULN in case of hepatic metastases), ▪ Total bilirubin ≤1.5 × ULN ° Renal function: ▪ Creatinemia clearance >50 ml/min (Cockcroft and Gault) • Patient with Public Health insurance coverage	• Patients with phenylketonuria • Patients with known meningeal or brain metastases • Patient previously treated for their metastatic cancer • Patient previously treated with oxaliplatin • Patient with specific contraindication or known hypersensitivity to spirulina • Patient with specific contraindication or known hypersensitivity to oxaliplatin. • Known allergy or hypersensitivity to antibodies or any preservatives if patient is treated with a monoclonal antibody combined to chemotherapy (bevacizumab or cetuximab or panitumumab or nivolumab), • Patient with clinically significant coronaries affection or myocardial infarction within 6 months prior to randomization. • Patient with peripheral neuropathy >1 (CTCAE scale version 5.0). • Patients with known dihydropyrimidine dehydrogenase (DPD) deficiency. • Patient with acute intestinal obstruction or sub-obstruction, history of inflammatory intestinal disease or extended resection of the small intestine or presence of a colic prosthesis. • Patient with unhealed wound, active oesogastric or duodenal ulcer, or bone fracture • Patient with an history of abdominal fistulas, trachea-esophageal fistulas or any other grade 4, gastro-intestinal perforations or non-gastrointestinal fistulas or intra-abdominal abscesses during the 6 months before randomization. • For patient treated with bevacizumab: patient with uncontrolled arterial hypertension (systolic pressure >150 mmHg and/or diastolic pressure >100 mmHg) with and without antihypertensive medication. Patients with high hypertension are eligible if antihypertensive medication lowers their arterial pressure to the level specified by the inclusion criterion. • Patient with an history of hypertensive crisis or hypertensive encephalopathy • Patient with other concomitant malignancy or history of cancer (except in situ carcinoma of the cervix, or non-melanoma skin cancer, treated with curative intent treatment) except if considered in complete remission for at least 2 years before randomization • Existence of any other pathology, metabolic problem, anomaly during the clinical examination or biological anomaly which may reasonable suspect an underlying pathology which would contra-indicate the use of the study medication or any other risk of complication related to the treatment. • Any treatment including an experimental drug, or participation in another clinical trial within 28 days before randomization. • Pregnant women, or women who could possibly be pregnant (or who expect to fall pregnant within 6 months of the end of treatment), or who are breast feeding are not eligible. • Men and women of child-bearing potential who do not accept to use a highly effective contraceptive (as per currently acceptable institutional standards) or abstinence during the study and for the 6 months after the last administration of the study treatments. • Persons deprived of liberty or under guardianship. • Psychological, familial, sociological or geographical condition potentially hampering compliance with the study protocol and follow-up schedule

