## Assignment of interventions: allocation

### Sequence generation {16a}

Randomization will be conducted blindly by center, neuropathy (stage 0 or 1), and age (< 65 years old and ≥ 65 years old). Wrongly enrolled randomized patients will not be replaced. It will be block balanced in a 1:1 ratio. The software used for the randomization is SAS version 9.4.

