## Data collection and management

### Plans for assessment and collection of outcomes {18a}

Motor nerve conduction will be investigated for the median, tibial and fibular nerves, evaluating standard parameters: compound muscle action potential distal latency, baseline-to-negative peak amplitude and area, and motor nerve conduction velocity. Sensory nerve conduction will be recorded for the median, radial, and sural nerves, with sensory action potential peak-to-peak measurement. This EDX protocol will be performed three times for each patient, at the enrolment visit, at M4 (i.e., D1 of the ninth chemotherapy cycle), and at the end of the trial, 28 days after the last dose of SLPC/placebo.

Furthermore, we paired the ONLS questionnaire with the EDX. The ONLS scale is a disability questionnaire with a score that ranges from 0 (no disability) to 12 (severe disability). It has been validated in 100 patients with inflammatory polyneuropathy. It has a strong correlation (r = 0.97) with the Overall Disability Sum Score [14] and is widely used by neurologists assessing peripheral neuropathy.

Patients will complete another questionnaire during the trial, to measure their quality of life: QLQ-C30 version three [16]. Comprising 30 different items (questions), it is made up of 8 multi-item functional (physical, role, emotional, cognitive, and social) and symptom (fatigue, pain, and nausea) scales, one global health status and quality of life (QOL) scale, and 6 single items (dyspnea, insomnia, appetite loss, constipation, diarrhea, and financial difficulties). It covers the majority of the core symptoms recommended for patient-reported outcome measurement in cancer clinical trials [17].

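### The nerve-conduction (EDX) comparison names two tests that carry no covariate, although every patient has a baseline EDX; adjusting for it would give a more precise estimate at almost no cost

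*Protocol article*

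**What the plan says.** The analysis of EDX is a single clause in the section on statistical methods for primary and secondary outcomes {20a}: "EDX data will be compared using Fisher’s exact test and the Wilcoxon-Mann-Whitney test". It names no parameter, visit or covariate, and does not say whether values or changes are tested.

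Other sections show what is available for that analysis:

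- **Repeated recordings.** Section {18a}: "This EDX protocol will be performed three times for each patient, at the enrolment visit, at M4", with a third recording at the end of the trial. Outcomes {12} lists EDX "at baseline, M4 and M9/termination visit", and the study schedule (Table 2) agrees.
- **Mainly continuous parameters.** For the motor nerves, section {18a} lists "compound muscle action potential distal latency, baseline-to-negative peak amplitude and area, and motor nerve conduction velocity"; sensory action potentials are also measured.
- **Stratified allocation.** Section {16a}: "Randomization will be conducted blindly by center, neuropathy (stage 0 or 1), and age".
- **A different approach for comparable outcomes.** In the same list in {20a}, "Progression of grades 3 and 4 neurological adverse events at baseline, M4, and M9" is analysed by mixed linear regression with a random centre effect, as is QLQ-C30.

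Section {20b} plans no additional analyses. Section {8} sets the status of any comparison between arms: "PROPERTY is a non-comparative, randomized (ratio 1:1), double-blind, multicenter placebo-controlled study".

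**The concern.** EDX is the trial's only instrumental measure of neuropathy; the others are grades or questionnaires. Nerve amplitudes, latencies and velocities differ between patients before treatment, and a baseline recording lets the analysis remove much of that spread. Fisher's exact test and the Wilcoxon-Mann-Whitney test compare two samples and have no place for a covariate. As written, the comparison therefore cannot adjust for the baseline value, the strata or centre.

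At stake is the precision of the EDX evidence. With at most 55 patients per arm, a real difference in nerve function could be left with a wide interval or missed. The two tests by themselves also give mainly p-values, which help less than an estimated difference in a trial not powered to compare its arms.

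**Working it through.** **The plan's own figure.** There is none to reproduce. The article gives no effect size, standard deviation (SD), correlation or power for EDX. Its sample size rests on a two-stage rule for neurotoxicity in the SLPC arm and has no bearing here.

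**Inputs.** From the article: 55 patients per arm and 20% loss to follow-up at 4 months (section {14}), so 55 × 0.8 = 44 per arm if the loss is taken off the 55. Assumed: correlation r between baseline and M4 of 0.5, 0.7 or 0.8, equal variances at both visits, and approximately normal data.

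**Variance of the arm difference, relative to follow-up values alone.**

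- Follow-up value: 1
- Change from baseline: 2(1 − r)
- ANCOVA on baseline: 1 − r²

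ANCOVA relative to follow-up values is therefore 1 − r². Relative to change scores it is (1 − r²) / [2(1 − r)] = (1 + r)/2. Interval width goes with the square root.

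| r | ANCOVA vs follow-up values | Interval narrower by | ANCOVA vs change scores | Interval narrower by |
|---|---|---|---|---|
| 0.5 | 1 − 0.25 = 0.75 | 1 − √0.75 = 13% | 1.5/2 = 0.75 | 13% |
| 0.7 | 1 − 0.49 = 0.51 | 1 − √0.51 = 29% | 1.7/2 = 0.85 | 1 − √0.85 = 8% |
| 0.8 | 1 − 0.64 = 0.36 | 1 − √0.36 = 40% | 1.8/2 = 0.90 | 1 − √0.90 = 5% |

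Change scores beat follow-up values only when 2(1 − r) < 1, that is, when r exceeds 0.5. In this large-sample arithmetic ANCOVA is at least as precise as either at every r.

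**What this means for power.** Assume a true difference of 0.5 SD and a two-sided 0.05 level. Power = Φ(0.5 / (s√(2/n)) − 1.96), where s is the square root of the relative variance above. For the Wilcoxon test n is multiplied by its efficiency under normality, 3/π. Example, Wilcoxon on follow-up values with 44 per arm: n = 44 × 0.955 = 42.0, √(2/42.0) = 0.218, 0.5/0.218 = 2.29, and Φ(0.33) = 63%.

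| Per arm | Analysis | r = 0.5 | r = 0.7 | r = 0.8 |
|---|---|---|---|---|
| 44 | Wilcoxon, follow-up values | 63% | 63% | 63% |
| 44 | Wilcoxon, change from baseline | 63% | 84% | 95% |
| 44 | ANCOVA | 77% | 91% | 97% |
| 55 | Wilcoxon, follow-up values | 73% | 73% | 73% |
| 55 | Wilcoxon, change from baseline | 73% | 91% | 98% |
| 55 | ANCOVA | 86% | 96% | 99% |

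**Validity of the stated test.** In 3,000 simulated trials for each r, with 44 per arm and no true difference, the Wilcoxon test on follow-up values rejected in 3.8% to 5.0% of trials. Its error rate is kept; only precision is lost.

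**The case against.** Four stronger readings are tempting, and the article supports none of them.

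- **That the baseline is ignored.** A reader might infer that raw M4 values will be compared. The text does not say so: a Wilcoxon test on change from baseline fits the same sentence and uses each patient's own baseline. The larger gains (29% and 40%) hold only for follow-up values.
- **That Fisher's test will be applied to categorised amplitudes.** Nothing says this. Naming both tests most naturally means Fisher for categorical findings and Wilcoxon for continuous ones.
- **That chance imbalance will produce false positives.** Allocation is randomized, and the test's error rate already covers chance imbalance, as the simulation shows. Clinical neuropathy above grade 1 is excluded, and the neuropathy stage, age and centre are strata. Subclinical EDX values are not, but that affects precision and does not create bias.
- **That the trial's conclusion is at risk.** EDX is one of several secondary outcomes in a trial declared non-comparative, and no stopping or success rule depends on it.

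It can also be said that the parameter, the visit and the derived variable belong in an analysis plan that is not shown. That is fair, and their absence is not the point here. The point is the method the article does name: neither test can take a covariate, on either reading of the tested variable. Choosing a valid rank test is not an error, but it is the less informative choice when the baseline has been collected for everyone.

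**Conclusion.** The point holds as one about precision. The stated tests are valid, but they are less precise than a baseline-adjusted comparison of data the trial already collects. For r between 0.5 and 0.8, adjustment would narrow intervals by about 13% to 40% against follow-up values, or by about 13% to 5% against change scores. The correlations are assumptions, and the figures also assume equal variances and roughly normal data. The power figures further assume a 0.5 SD effect. The article does not settle which of the two ranges applies. The consequence is confined to the EDX evidence.

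**What to change.** In {20a}, replace the EDX clause with a statement along these lines:

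- Each continuous EDX parameter is compared between arms at M4 and at the end of the study with a model containing the baseline value of that parameter, the neuropathy stratum, the age stratum and centre, with centre as a random effect as for the other outcomes.
- If a parameter is expected to be skewed, the log or rank scale is specified in advance.
- The adjusted difference is reported with a 95% confidence interval.
- Fisher's exact test is used only for categorical EDX findings.

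The cost is a short wording change and a little more modelling. No new data are needed. The change should be made before unblinding.

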**Fig. 2 Fig2:**
[figure not shown]
Schedule of trial treatment in chemotherapy cycles

After induction chemotherapy, the patients on maintenance therapy or targeted therapy will continue to take spirulina for six cycles (3 months) after the last cycle of oxaliplatin (Fig. 2B). The same schedule will be applied for the patients who are not on maintenance chemotherapy (Fig. 2C). The complete trial schedule is shown in Table 2.

**Table 2 Tab2:** Study schedule

Assessments	Inclusion visit D-30 to D-4	Cycle 1	Cycle 1 to 12		Cycle 13 to 18	End of study visit / 28 days after last day of PHYCOCARE® /PLACEBO
		D-3 to D-1	D1 to D3	D4 to D14	D1 to D14	
Informed consent	X					
Medical History	X					
Clinical examination (Performance status (ECOG), vital signs, symptoms)	X		X (D1)		every 28 days	X
ONLS questionnaire	X		at M4 (C9D1)			X
QLQ-C30 questionnaire	X		at M4 (C9D1)			X
EDX	X		at M4 (C9D1)			X
Randomisation	X					
Scanner	at D-42					
PHYCOCARE® or placebo treatment		X		X	X (days without chemotherapy)	
Oxaliplatin-based chemotherapy			X			
Chemotherapy maintenance regimen					If applicable	
Adverse events (AE)		AE assessed at each patient visit				X
Treatment adherence (patient diary)		Compliance assessed at each patient visit				X

Note that the oxaliplatin dose is 85 mg/m^2^ and the dose adjustment is shown in Table 3.

**Table 3 Tab3:** Oxaliplatin dose adjustement

Scale	NCI-CTC grading for neuropathy
Grade 1	Asymptomatic, loss of deep tendon, reflexes, or paresthesia (including tingling), but not interfering with function
Grade 2	Sensory alteration or paresthesia (including tingling) interfering with function, but not ADL
Grade 3	Sensory alteration or paresthesia interfering with ADL
Grade 4	Disabling

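### The planned quality-of-life test names toxicity grades that the QLQ-C30 does not have, and PFS and a response rate are analysed without being listed as outcomes or supported by a scheduled scan after baseline

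*Protocol article*

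**What the plan says.** **Quality of life.** Objectives {7} lists quality of life by the EORTC QLQ-C30 as a secondary objective. Outcomes {12} lists "Quality of life questionnaire: QLQ C30 at baseline, M4 and M9/termination visit". The one item in Statistical methods {20a} that tests it reads "Progression of grades 3 and 4 neurological QLQ C30 at baseline, M4, and M9 (or at the last visit if earlier"), by mixed linear regression with centre as a random effect. Plans for assessment {18a} describes the instrument: "Comprising 30 different items (questions), it is made up of 8 multi-item functional" and symptom scales, then "one global health status and quality of life (QOL) scale, and 6 single items (dyspnea, insomnia, appetite loss, constipation, diarrhea, and financial difficulties").

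**PFS and response.** The last item of {20a} promises a Kaplan-Meier median PFS and a response rate with a 95% confidence interval. Of the visit schedule, Intervention description {11a} says "The complete trial schedule is shown in Table 2". The scanner row of that table has a single entry, D-42, in the inclusion column.

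**Neurological adverse events.** Another item of {20a} tests "Progression of grades 3 and 4 neurological adverse events at baseline, M4, and M9 (or at the last visit if earlier"). Table 1 under Eligibility {10} excludes a "Patient with peripheral neuropathy >1 (CTCAE scale version 5.0").

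**The concern.** Each of these secondary analyses was checked against the section that should supply its data: the instrument description, the outcome list, the visit schedule and the entry criteria. They do not fit together.

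For quality of life, the variable to be tested does not exist. If the line is repaired only after the data are seen, any of the questionnaire's scores could become the reported one. For PFS and response, the article commits to results that it neither lists as outcomes nor schedules assessments for, and the word response has another meaning elsewhere in the same article. For grade 3-4 neurological events, one of the three time points in the model cannot vary for the toxicity of main interest.

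**Working it through.** The plan gives no figure to reproduce here. The check sets the sections side by side and counts.

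**1. QLQ-C30**
- Scores described in {18a}: 5 functional scales (physical, role, emotional, cognitive, social) + 3 symptom scales (fatigue, pain, nausea) = 8 multi-item scales. Adding 1 global scale and 6 single items gives 8 + 1 + 6 = 15.
- Of these 15, the number with a grade 3 or 4 is 0, and the number labelled neurological is 0.
- The item in {20a} asks for grades 3 and 4 of a neurological quantity. No score in the description matches.
- The adverse-event item in the same list begins "Progression of grades 3 and 4 neurological adverse events at baseline, M4, and M9". The two items have the same opening, visits and model, and differ only in the thing measured. A copying slip is the likely explanation.
- With the stray words removed, what remains is QLQ-C30 at three visits by a mixed linear model. That agrees with Table 2 and Outcomes {12}, but no score is named.

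**2. PFS and response rate**
- Mentions in Objectives {7}: 0. Mentions in Outcomes {12}: 0. Additional analyses {20b} says that none are planned.
- Scans in Table 2 after baseline, over 18 cycles: 0. The one scan serves the entry criterion that disease sites be evaluated within 42 days before cycle 1.
- Progression or response criterion printed: none.
- Meaning of response elsewhere: Sample size {14} sets a null response rate of 0.60 for neurotoxicity, and Interim analyses {21b} defines a responder as a patient with grade 1 neurotoxicity. Placement beside PFS suggests tumour response, but the text does not say so.

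**3. Grade 3-4 neurological events at baseline**
- Entry allows peripheral neuropathy of grade 0 or 1 only, and Sequence generation {16a} stratifies on stage 0 or 1, which agrees.
- Among eligible patients, grade 3-4 peripheral neuropathy at baseline is therefore 0 of 55 per arm, or 0 of 110. A time point at which every value is zero carries no information on progression or on a difference between arms.
- At M4 and M9 no such limit applies, and events can be observed.

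**The case against.** The best defence is that little here is substantive. The QLQ-C30 line is a typing error whose intent can be guessed. The scores are collected, and {20a} promises point estimates and confidence intervals for all variables. The choice of scales is commonly left to an analysis plan, which is not shown. Much of this stands. A reader might infer that the quality-of-life objective would yield no result at all, but descriptive estimates would still be produced. What does not stand is that the line is merely silent: it names a wrong variable, and correcting it requires someone to choose a score.

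On PFS, routine-care scans may well be done and recorded. Adverse event reporting {22} lists disease progression among expected events, so progression may be captured that way. PFS is only estimated and plotted, not tested. This also stands. The documents do not show that imaging goes uncollected, and they do not present PFS as a check on whether the supplement affects tumour control. The mismatch between the printed analysis, the outcome list and the schedule remains.

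On neurological events, three stronger readings are tempting, and the documents support none of them:
- **That grade 2 is discarded.** Grade 2 or above is the main analysis in {20a}, and a separate item compares adverse events between arms with no grade limit.
- **That grade 3-4 cannot be obtained.** It can be observed at M4 and M9. A zero baseline is ordinary for a toxicity outcome, and the exclusion names peripheral neuropathy, not every neurological event.
- **That the comparison has too little power.** Any such figure needs prevalences that the article does not give, and Trial design {8} already says that the trial is not powered to compare the arms.

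**Conclusion.** The point holds in three parts of unequal weight.

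1. The quality-of-life item is wrong as printed. None of the 15 scores described carries a grade or a neurological label, so the stated secondary objective has no executable test. This is the main part.
2. PFS and a response rate are analysed but not listed as objectives or outcomes. The schedule has no scan after baseline, and response is ambiguous. This is an inconsistency to resolve. It does not prove that the data will be missing.
3. The baseline visit adds nothing to the grade 3-4 model for peripheral neuropathy. This is minor.

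The primary endpoint is untouched. The conclusion rests on the article's own description of the QLQ-C30 and on taking Table 2 as complete, as the article says it is. The zero at baseline assumes that the entry criterion is met. The full protocol may already settle parts of this, in which case the printed text needs only to be brought into line.

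**What to change.** 1. Replace the QLQ-C30 item with change from baseline, at M4 and M9, in named scale scores. One should be designated as the main score (global health status, for example), and the mixed linear regression with a random centre effect kept. This is a change of wording that uses data already collected.
2. For PFS and response, take one of two routes. Either state that response means tumour response, list both under Outcomes {12}, and record in the eCRF the date and result of each routine-care tumour assessment under one stated criterion; or delete both from {20a}. The first route costs a few eCRF fields and no added imaging. The second costs nothing.
3. Analyse grade 3-4 neurological events at M4 and M9 as post-baseline outcomes, adjusted for the baseline neuropathy grade (0 or 1) already used in the randomisation. This is also wording only.

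All three should be settled before unblinding, so that the choice of score and criterion cannot depend on the results by arm.
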